## Abstract

**Background:**

Besides classical approaches for treating depression, physical activity has been demonstrated to be an effective option. Bouldering psychotherapy (BPT) combines psychotherapeutic interventions with action-oriented elements from the field of climbing. The aim of this study is to investigate the effectiveness of BPT compared with a home-based exercise program (EP - active control group, superiority trial) and state-of-the-art cognitive behavioural therapy (CBT – non-inferiority trial).

**Methods:**

The study is being conducted as a multicentre randomised controlled intervention trial at three locations in Germany. Participants are being randomised into three groups: BPT, CBT, or EP, each with a 10-week treatment phase. A power analysis indicated that about 240 people should initially be included. The primary outcome of the study is the Montgomery and Asberg Depression Rating Scale (MADRS) directly after the intervention. Additional measurement points are located three, six, and 12 months after the end of the intervention. The data are being collected via computer-assisted telephone interviews. Statistical analyses comprise regression analyses to test for the superiority of BPT over EP. To test for the non-inferiority of BPT and CBT, a non-inferiority margin of 1.9 points in the Patient Health Questionnaire (PHQ-9) and two non-inferiority margins for the MADRS (half of the two smallest Cohen’s d values from the current meta-analyses) was predefined. The mean difference between CBT and EP is being used as a supplementary equivalence margin.

**Discussion:**

This is the first study to investigate the effect of a bouldering psychotherapy (BPT) on outpatients’ depressive symptoms compared with mere physical activity (superiority analysis) and state-of-the-art cognitive behavioural therapy (CBT, non-inferiority analysis).

Methodological strengths of the study are the elaborated, multicentred, randomised, controlled design. Assessors are blinded with regard to group allocation which leads to high objectivity. The study is conducted in a naturalistic setting, which leads to high external validity. Methodological limitations might be the clinical heterogeneity of the sample, which may dilute the intervention effects.

**Trial registration:**

ISRCTN12457760 (Registration date: 26 July 2017, retrospectively registered).

## Background

With a lifetime prevalence of 12.5 [1] and a 12-month prevalence of 3.2% [2], depression is one of the most common diseases worldwide. Estimations of the WHO indicate that by 2020, depression will be the second leading cause of health impairment (after cardiovascular diseases), and by 2030, it will be the most frequent impairment in industrialised nations [3, 4]. In line with clinical guidelines for the treatment of depression, medication and psychotherapy are the approaches that are most commonly recommended [5, 6]. The gold standard in the psychotherapeutic treatment of depression is cognitive behavioural therapy. With effect sizes (Hedges’ *g*) ranging from 0.55 to 0.98 (moderate to large effects) in metaanalyses [7] it has shown to be at least as effective as antidepressants [5, 8]. Especially regarding psychotherapy, there is a vast gap between supply and demand owing to a lack of therapeutic resources. In the UK, only 10% of the people suffering from anxiety or depression receive psychological treatment [9]. Another challenge is that it is difficult to engage and retain patients in psychological care. Only about 52.2% of depressive individuals living in Germany actively seek professional help [10]. Also in the UK, only half of the patients who receive psychological treatment from a general practitioner attend two or more sessions [11]. These findings highlight the need for new therapies that are as effective as established treatment options and at the same time easier for patients to access, more attractive, and less stigmatized. Besides the classical approaches of psychotherapy and medication, physical activity has also been demonstrated to be an effective treatment option [12–15]. On the basis of effect sizes (Cohen’s *d*) that have been reported to lie between 0.62 and 0.82 (moderate to strong effects), physical activity has been added to the German guidelines for the treatment of depression as a supplementary therapeutic method [5].

One type of physical activity that has become increasingly popular in recent years and is spreading all over the world is climbing, notably bouldering. Bouldering means climbing without a rope on rocks or artificial indoor climbing walls at a height that permits the climber to jump off. Climbing halls provide climbing routes with different levels of difficulty (coded with different colours), enabling persons with varying levels of physical fitness to boulder together without feeling over- or unchallenged. Climbing and bouldering have gained increased attention in clinical practice and are nowadays often used as part of the overall treatment plan for health problems [16, 17]. Earlier research showed that therapeutic climbing enables the stimulation of cognitive, emotional, and physical development as well as learning processes [18]. Furthermore, it can offer a person an opportunity to become more active and can be a learning opportunity in which a person can set realistic goals. Finally, mastering “bouldering problems” has been found to have a positive impact on a climber’s self-esteem [19]. Owing to the different levels of difficulty, even beginners can experience a sense of achievement, which sets up positive reinforcement processes that might be especially helpful in the treatment of depression [18].

Existing studies on the therapeutic effects of climbing and bouldering have suggested that climbing/bouldering has positive effects on health issues such as chronic pain [20–22], multiple sclerosis [23], cerebral palsy [24], and severe haemophilia A [25] as well as on psychological problems such as ADHD [19, 26], anxiety disorders [19], and eating disorders [19]. Such effects might be moderated by an increase in cognitive functioning [16, 19], self-esteem, self-confidence, self-efficacy [19, 27], and social competences [16, 19]. Unfortunately, existing studies have suffered from various methodological problems: Some studies were case studies or descriptive reports with low case numbers [16, 19, 28]; some used only self-developed, unvalidated questionnaires or unstandardised interviews [29]; most did not randomly assign participants to intervention or control groups [30], and some used no control group at all [31]. Thus, a systematic review of existing randomised controlled studies on climbing/bouldering for preventing and treating health problems found only very low-quality evidence of improvements through therapeutic climbing and led to the conclusion that future studies should have a sufficient sample size, should use patient important outcomes, should be registered prospectively, and finally, should be reported in accordance with the CONSORT statement [31].

With respect to treating depression, some case reports and observational studies have reported positive effects of climbing and bouldering on depressive symptoms [16, 19, 30, 32]. Recently, a controlled – but not randomised – trial including 40 in-patients suffering from major depressive disorder showed the impact of rock climbing on acute emotion regulation strategies [17]. Positive affect and coping emotions significantly increased, while negative affect and depressiveness significantly decreased directly after the climbing session in comparison with a relaxation control group. Between 2013 and 2015, our work group conducted a randomised controlled pilot study to investigate the effect of a bouldering intervention on depressive symptoms. A total of 94 patients were randomly assigned to either a waitlist control group or an intervention group, which included eight sessions of bouldering psychotherapy. Different health outcomes were assessed with standardised psychological self-report questionnaires before and after the eight-week intervention period as well as 16 weeks after the end of the therapy. Participants in the intervention group reported a significant reduction in depressive symptoms compared with the control group, even when other types of physical activity was controlled for [33, 34]. With an effect size (Cohen’s *d*) of 0.77 (moderate effect) the effect of the bouldering intervention on depressive symptoms was comparable to other short-term group therapies [35] and to physical activity (see above).

## Methods

### Aims and hypothesis

The aim of the current study, StudyKuS (Studie**KuS** – **K**lettern **u**nd **S**timmung; engl. Climbing and Mood), is to investigate a) whether our newly developed bouldering psychotherapy is more effective in reducing depressive symptoms than physical activity alone and b) whether the effect of our therapy is comparable to current state-of-the-art group psychotherapy. For this purpose, we are comparing our bouldering psychotherapeutic intervention (BPT) with a state-of-the-art cognitive behavioural group therapy (CBT) and a home-based exercise program (EP - active control group) using a randomised and controlled but nevertheless naturalistic design.

#### Research hypothesis

I.Bouldering psychotherapy (BPT) leads to a significantly greater reduction in depressive symptoms in outpatients with depression than mere physical activity in the form of a home-based exercise program (EP).II.The positive effect of bouldering psychotherapy (BPT) on reducing depressive symptoms in outpatients with depression is not inferior to the effect of cognitive-behavioural psychotherapy (CBT).

In this article, we describe the StudyKuS study protocol, which serves as a reference for forthcoming papers that report the results of the study.

### Study design and setting

To test the research hypotheses, a randomised, controlled, multicentre, prospective longitudinal study with three arms is being conducted. Recruiting for the StudyKuS began in 2017 in three different regions in Germany: a) the Erlangen/Nuremberg/Fuerth region (metropolitan region of three cities), b) the Weyarn region (rural area surrounding Munich), and c) the Berlin (capital) region. Each intervention is being carried out by two therapists (with the exception of the EP, which is supervised by the study’s headquarters) over a period of 10 weeks in groups with a maximum of 11 participants. All of the three interventions in one region are taking place during the same time period and are being conducted in consecutive waves – with four waves in the Erlangen/Nuremberg/Fuerth region as well as the Weyarn region and two waves in the Berlin region. Participants in one region and one wave are randomly allocated to one of the three groups (BPT, CBT or EP). Data are being collected via computer-assisted telephone interviews (CATIs) before and directly after the intervention as well as three, six, and 12 months after the treatment. A data monitoring and safety board (DMSB) is established ([name]) and supervises study conduction and severe adverse events (SAEs). All procedures have been approved by the Friedrich-Alexander-Universität Erlangen-Nürnberg Ethics Committee (Ref. 360_16 B). The participant timeline is presented in Fig. 1. Trial Registration Data are presented in Table 1 (ISRCTN12457760, Registration date: 26 July 2017, registered retrospectively).

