### Sample size estimation

A power analysis was computed on the basis of the authors’ previous experience with the BPT in the pilot study in which a Cohen’s d of 0.77 was reached [33]. To address Hypothesis I, a slightly lower effect size of 0.6 was assumed. Thus,61 patients will be needed in the BPT group and 61 patients in the EP group (alpha = .05, power = .9).

To address Hypothesis II, a non-inferiority margin of 1.9 points (SD = 3.8) on the PHQ-9 (as proposed in the literature [36]) was used, which resulted in a total of 69 patients in the BPT group and 69 patients in the CBT group (alpha = .05, power = .9). Thus, there should be 61 patients in the EP group, 69 patients in the BPT group, and 69 patients in the CBT group, for a total of 199 patients. To account for dropouts between t0 and t1, 20% more patients are added (based on the drop-out-rate of our pilot study), resulting in 40 additional patients for a total of 239.

Therefore, 10 waves in three therapy centres (two waves in Berlin, four waves in Weyarn, four waves in Erlangen) were planned. Each wave was designed to include 24 participants on average, of which 20 were expected to complete the respective intervention.

Also from the data of the pilot study, in which similar recruitment modalities were applied, a failure of approx. 40% of patients who do not meet the inclusion criteria must be expected. This means that a total of approximately 400 patients should be screened.

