### Interventions

#### Bouldering psychotherapy (BPT)

Bouldering is defined as climbing to moderate heights (up to around three metres) without the use of ropes or harnesses. The great variety of difficulty levels in bouldering gyms (usually marked by different colours) allows patients with different physical fitness levels to easily boulder together in one group without feeling over- or unchallenged. Our newly developed bouldering intervention is a combination of bouldering and psychotherapy and consists of 10 consecutive sessions of 2 hours, taking place in a bouldering gym once a week in the late afternoon. The intervention takes place in a group of about 10 patients who are supervised by two climbing therapists. We have teams of two therapists in each study region, but the compositions of personnel may vary across the different waves of therapy because the therapists are also balancing other commitments. All in all, we engage nine climbing therapists for the BPT groups. All but one of the climbing therapists are either psychotherapists or are in the process of completing their psychotherapy hours (psychotherapists must have a master degree in psychology plus an additional 4200 h of further education as a psychotherapist according to German law; the one exception has an Master of Science in Health Science including sports psychology) and are experienced in bouldering and rock climbing (their climbing ability is rated at a minimum of grade 7 on the UIAA (Union Internationale des Associations d’Alpinisme) scale; one person on each team had received advanced training from the German Alpine Association or the Austrian Institute for therapeutic climbing). Prior to the intervention, all of the therapists are thoroughly trained in bouldering techniques, safety rules, and didactic elements by a professional bouldering instructor and in the implementation of the bouldering therapy manual by two members of the study’s headquarters, both of whom had obtained qualifications in “therapeutic climbing”.

Each of the 10 sessions focuses on a specific psychological topic that we consider to be relevant in the development and maintenance of depression. An overview of the specific subjects covered in the 10 therapeutic sessions is provided in Table 2.

**Table 2 Tab2:** Overview of the bouldering therapy sessions

Session	Topic
1	Introduction to bouldering and mindfulness
2	Physical feeling and the body’s centre of gravity
3	Healthy handling of limitations

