#### Cognitive behavioural therapy (CBT)

The CBT group is also manualised and follows the treatment plan of classical cognitive-behavioural therapy. It combines the psychoeducational parts of Schaub et al. [38] with specific exercises as well as elements of the strategic behavioural therapy (SBT) by Sulz [39] and elements of the short-term concept by Hautzinger & Kischkel [40]. At the beginning and end of each session, mindfulness-based techniques and relaxation methods are integrated. Comparable to the BPT, the CBT intervention consists of 10 consecutive sessions of 2 hours, takingplace once a week in the late afternoon in a group of about 10 patients with teams of two therapists in each study region (all in all, eight different therapists). Comparable to the qualification of the BPT therapists, all CBT therapists are either psychotherapists or psychologists who are completing their psychotherapy hours and are experienced in the treatment of depression. Prior to the intervention, all of the therapists are thoroughly trained in the implementation of the CBT manual by two members of the study’s headquarters. Similar to the BPT intervention, each of the 10 sessions focuses on a specific psychological topic (see Table 3).

**Table 3 Tab3:** Overview of the cognitive behavioural therapy sessions

Session	Topic
1	Introduction to CBT therapy and psychoeducation
2	Psychoeducation on depression and dysfunctional beliefs
3	Identifying and working on individual dysfunctional beliefs
4	Behavioural activation/ activity scheduling
5	Social relationships I
6	Social relationships II
7	Cognitive techniques I
8	Cognitive techniques II
9	Lessons learned: Transforming dysfunctional beliefs
10	Reflecting on lessons learned and on transferring them to daily life

Therapists in all of the three therapy centres follow a manual including a fixed schedule for each session. Each session consists of three main parts – comparable to the BPT manual: a) introduction – which consists of a mindfulness exercise, a short interactive repetition of the last session, and a review of the home-based exercises; b) main part – in which the specific topic is interactively developed using flipcharts, exercise sheets, and small-group work; and c) closure – where worksheets are handed out, home-based exercises are discussed, and a relaxation exercise (progressive muscle relaxation according to Jacobsen) [41] is carried out.

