#### Hypothesis I: superiority of BPT over EP

The primary outcome variable is the MADRS. To test the first hypothesis, t-tests for independent groups of change scores (pre-post) will be performed between the BPT and EP groups. In addition, multivariate analyses (ANOVAs and multiple linear regression analyses) will be calculated. To control for the effects of confounders, demographic variables as well as other therapeutic treatments patients used outside of the treatments offered in the study (e.g. antidepressive medication, psychotherapy, offers to participate in additional sports) will be included in the regression analyses.

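### BPT and CBT are given in therapist-led groups, but the sample sizes and the Hypothesis I t-test assume independent patients; non-inferiority power falls below the stated 90%, and both comparisons risk inflated error

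*Protocol article*

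**What the plan says.** **Delivery.** Under Study design and setting, the interventions other than the exercise programme (EP) are each run by two therapists, "over a period of 10 weeks in groups with a maximum of 11 participants". The section on bouldering psychotherapy (BPT) says "The intervention takes place in a group of about 10 patients who are supervised by two climbing therapists", and the section on cognitive behavioural therapy (CBT) likewise has weekly sessions "in a group of about 10 patients with teams of two therapists in each study region". Therapists are shared across groups: "we engage nine climbing therapists for the BPT groups", and eight therapists cover CBT. EP is done individually at home.

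**Number and size of groups.** Sample size estimation states that "10 waves in three therapy centres (two waves in Berlin, four waves in Weyarn, four waves in Erlangen) were planned" and that "Each wave was designed to include 24 participants on average, of which 20 were expected to complete the respective intervention".

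**Sample size.** Hypothesis I assumes d = 0.6 and asks for 61 patients each in BPT and EP. Hypothesis II uses a 1.9-point PHQ-9 margin with SD 3.8, "which resulted in a total of 69 patients in the BPT group and 69 patients in the CBT group (alpha = .05, power = .9"). The planned arms are therefore 69 BPT, 69 CBT and 61 EP. The only inflation is 20% for dropout.

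**Analysis.** For Hypothesis I, "t-tests for independent groups of change scores (pre-post) will be performed between the BPT and EP groups", supplemented by ANOVA and regressions that adjust for demographic variables and outside treatment. For Hypothesis II, a between-group difference is set against margins, and no test or standard error is named. The Data analysis section mentions no term for therapy group or therapist.

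**The concern.** Patients who spend ten weekly two-hour sessions in the same group, with the same two therapists and with interactive exercises, can be expected to have correlated outcomes. The design is partially nested: BPT and CBT patients sit within groups, and EP patients do not. A calculation that treats all patients as independent gives standard errors that are too small wherever a clustered arm is involved.

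The consequences differ by hypothesis. In BPT versus EP only one arm is clustered. In BPT versus CBT both are, and an interval that is too narrow makes non-inferiority easier to declare, so the error favours the trial's hoped-for conclusion.

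**Working it through.** **Inputs from the protocol.** 10 waves, hence about 10 groups in each of BPT and CBT. By the planning figures, a group has 24/3 = 8 patients randomised, 20/3 = 6.7 completing and 69/10 = 6.9 analysed. The intervention sections describe about 10. I use m = 6.9, the smallest effect consistent with 69 analysed patients in 10 groups.

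**Assumed input.** Within-group ICC of 0.02, 0.05 or 0.10; the protocol gives none.

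**Step 1: reproduce the stated sizes under independence.**
- Hypothesis I: n = 2(1.960 + 1.282)²/0.6² = 58.4, so 59 per arm (60 by the exact t-test), against the stated 61. This fits a two-sided 5% test; a one-sided test would need 48.
- Hypothesis II: n = 2(1.645 + 1.282)² × (3.8/1.9)² = 68.5, so 69 per arm, an exact match. This fits a one-sided 5% test with a true difference of zero; one-sided 2.5% would need 85.

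Both correspond to a design effect of 1.

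**Step 2: design effect.** DE = 1 + (m − 1) × ICC = 1 + 5.9 × ICC, which gives 1.118, 1.295 and 1.590.

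**Step 3: Hypothesis II (both arms clustered, 69 per arm).**
- SE = 3.8 × √(2 × DE/69).
- Power (normal) = Φ(1.9/SE − 1.645).
- One-sided error without a group term = 1 − Φ(1.645/√DE).
- Small-sample power uses the noncentral t with noncentrality 1.9/SE. Twenty group means less two arm means leave 18 df. Fitting the 10 region-wave blocks as fixed effects leaves 20 − 10 − 1 = 9 df.

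| ICC | DE | SE | Power, normal | Power, 18 df | Power, 9 df | One-sided error, no group term | Correct interval wider by √DE |
|---|---|---|---|---|---|---|---|
| 0 | 1.000 | 0.647 | 90% | 88% | 86% | 5.0% | 1.00 |
| 0.02 | 1.118 | 0.684 | 87% | 85% | 82% | 6.0% | 1.06 |
| 0.05 | 1.295 | 0.736 | 83% | 80% | 77% | 7.4% | 1.14 |
| 0.10 | 1.590 | 0.816 | 75% | 72% | 69% | 9.6% | 1.26 |

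The ICC = 0 row shows that part of the loss in the two df columns comes from the small number of groups rather than from the ICC.

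**Step 4: Hypothesis I (BPT clustered, EP not, 69 versus 61).**
- Naive SE in SD units: √(1/69 + 1/61) = 0.1757.
- Correct SE: √(DE/69 + 1/61) = 0.1805, 0.1875 and 0.1986.
- Two-sided error of the t-test: 2 × [1 − Φ(1.960 × 0.1757/correct SE)] = 5.6%, 6.6% and 8.3%.
- Power: Φ(0.6/correct SE − 1.960) = 91%, 89% and 86%, against 93% at ICC 0.

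**Step 5: sensitivity to group size.** With m = 8, Hypothesis II power (normal) is 87%, 81% and 73%, and unadjusted one-sided error is 6.2%, 7.8% and 10.4%. With m = 10, the figures are 86%, 79% and 69%, and 6.5%, 8.6% and 11.6%.

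**The case against.** Several counter-arguments carry weight.

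- **The size rests on an assumed ICC.** This stands. At 0.02 the effect is modest: one-sided error of about 6% and power of 85% to 87% before blocks are fitted. Only the direction is certain for a positive ICC.
- **No Hypothesis II test is named.** This stands too. A reader might infer that the independent-groups t-test is also planned for non-inferiority. The protocol names it only for Hypothesis I and the secondary outcomes, and an analysis plan not shown could supply a suitable model. The Hypothesis II error rates are therefore conditional on an analysis without a group term. The 69 per arm, however, is fixed in this document without allowance for clustering.
- **Hypothesis I power is hardly affected.** A reader might infer that 90% power fails for both hypotheses. It does not: 69 BPT patients are planned rather than the 61 required, EP is unclustered, and power stays near 90% for small ICCs.
- **Randomisation within region and wave offsets some of the inflation.** Effects shared by the arms of a wave cancel in the contrast, while an unadjusted test still counts them as variance. With an assumed wave share of 5% of the variance, Hypothesis II error at ICC 0.05 falls from 7.4% to 6.9%. This is a small correction that leaves the point intact.
- **The power figures concern the PHQ-9 margin only.** True. The MADRS margins of d = 0.2 and 0.34 have about 32% and 64% power at 69 per arm even without clustering; that is a separate matter.

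**Conclusion.** The concern holds in a limited form. The design is partially nested, the stated sample sizes correspond to independent patients, and the named Hypothesis I test ignores therapy groups.

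With about 7 analysed patients per group and an assumed ICC of 0.02 to 0.10:
- the Hypothesis I t-test has a true two-sided error of about 5.6% to 8.3%, with no power failure claimed for small ICCs;
- Hypothesis II does not have its stated 90% power at the 1.9-point PHQ-9 margin, but about 87% to 75% by normal approximation, or 82% to 69% with 9 df;
- any Hypothesis II analysis without a group term would have a one-sided error of about 6% to 10%, towards declaring non-inferiority.

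Confidence is high for the direction and depends on the assumed ICC for the size. Correlation between groups that share a therapist is not included in these figures.

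**What to change.** - Analyse Hypotheses I and II with a linear mixed model that has a random intercept for therapy group (region by wave by arm) in BPT and CBT only, none in EP, and small-sample degrees of freedom.
- State whether the region-wave blocks enter as fixed effects, and compute power with the matching df: about 9 for BPT versus CBT with the blocks, about 18 without.
- Because therapists work across waves and team composition may vary, add a sensitivity analysis at therapist level.
- Restate Hypothesis II power over a declared ICC range, for example as in the table above, and reconcile the planned group size (8 randomised per group by the planning figures, about 10 in the intervention descriptions).

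The cost is analysis work only. Group membership follows from how the therapies are delivered, and the trial registration table lists recruitment as complete, so no additional patients are asked for. The downside is wider intervals and a lower stated power for non-inferiority.
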